**October, 2011**

**1-INTRODUCTION**

 In physiological conditions, the upper airways heat and humidify the inhaled air. During the inspiration, the air reaches the alveoli at body temperature (37°C) with 100% relative humidity (RU) and 44 mg H2O.L-1 absolute humidity (AH)1. The fresh gas flow (FGF) used during anesthesia is cold and dry. During tracheal intubation, the functions of the nose and the other upper airways are bypassed. If the humidification and heating of inhaled gases are not adequate, functional impairment occurs in the airway mucosa, by changing the cilia movement and increasing the mucus viscosity, which can lead to cilia and mucous destruction, increased airway resistance, changes in ventilation-perfusion ratio, microatelectasias, decreased lung compliance and functional residual capacity due to the changes of pulmonary surfactant, besides inflammatory reactions, ulcerations in the mucous membrane and dehydration, predisposing the formation of plugs that block the airways and the tracheal tube2-6. Thus, during artificial ventilation under tracheal intubation, heating and humidifying of the inspired gases are essential to ensure the integrity of the airways and the preservation of mucociliary function and gas exchange4,7.

There is disagreement regarding the ideal values of heating and humidification of inhaled gases, but it is necessary to establish limits of heating and humidification of the inhaled gases to prevent mucosal respiratory lesions8. An experimental study, performed in dogs who underwent tracheal intubation and mechanical ventilation for three hours, showed the effects of warming and humidifying inspired gases, according to the histological changes of the mucosal epithelium of the tracheobronchial tree to optical microscopy. The authors concluded that the temperature and AH of inspired gases must not exceed 36°C and 36 mg H2O.L-1, respectively, and should not have temperature below 27°C or AH below 23 mg H2O. L-1 9.

The use of low FGF during inhalation anesthesia has increased in recent years due to its important advantages, such as lower inhaled anesthetics consumption, more effective heating and humidification of the inspired gas and significant reduction of environmental pollution10-12. However, the use of low FGF has disadvantages that include the need for greater attention and anesthesiologist's care due to the difficult rapid change of the inspired concentration of inhaled anesthetic, most likely to hypercarbia production by the quickest exhaust system carbon dioxide absorption and possible accumulation of undesirable gases such as carbon monoxide, acetone, methane, and toxic metabolites of anesthetic agents12 requiring periodic "washing" of the breathing system at high FGF for a few minutes.

The reduction in the FGF leads to better utilization of heat and moisture from exhaled air and that is generated in the canister reservoir, through the CO2 neutralization reaction by soda lime, which is exothermic and leads to water training13-15. Several authors used low FGF with variable efficacy in relation to the heat and moisture inhaled gases levels10,14-17, especially when combined with the addition of a heat and moisture exchanger (HME) in the breathing circuit10,14. The different results in the studies maybe explained by different configurations of the breathing systems of the anesthesia machines, the different methods used for measuring moisture in the inspired gases, the different performances of the HMEs18, 19 and the FGF rate used10.

The operating room (OR) temperature directly influences the heat and moisture of the inhaled gases at different anesthesia workstations due to the low thermal insulation (TI) of silicone tubing used in the anesthetic breathing circuit14,15.

The Fabius GS Premium anesthesia workstation (Dräger Medical, Lübeck, Germany) has a built-in hotplate to heat the gases in the breathing circuit. In this anesthesia workstation breathing system, the exhaled gases move through the hotplate and cross the soda lime once before mixing with the cold and dry FGF. The mixed gases are then pulled by the plunger to fill the ventilator. After opening the inspiratory valve, the ventilator plunger sends the gaseous mixture to the inspiratory limb of the respiratory circuit, where it is warmed a second time by the built-in hotplate. The temperature and humidity of the inhaled gases coming from this anesthesia machine have not yet been investigated. It may be expected that the hotplate would warm the inhaled gases coming from this workstation.

The Primus anesthesia workstation (Dräger, Lübeck, Germany) also has a built-in hotplate; however, unlike the Fabius GS Premium, only the expiratory limb is warmed14. A study using this machine with a low-flow breathing system showed a lower temperature (25.3 ± 1.4°C) and AH (20.5 ± 3.6 mg H2O.L-1) of the inspired gas after 120 minutes of connection of the patient to the breathing circuit14.

The minimum AH values of the inhaled gases should be 30 mg H2O.L-1 for patients under tracheal intubation in intensive care unit19,20 and 20 mg H2O.L-1 in patients undergoing general anesthesia with tracheal intubation to avoid dehydration of the respiratory tract19.

**2-STUDY HYPOTHESIS**

Humidification and heating of the gases in the breathing circuit from low-flow Fabius GS Premium Dräger anesthesia workstation may not be enough to provide the minimum humidity level of the inspired gases, which can be directly influenced by the OR temperature. We will test the hypothesis that the use of a HME, which retains heat and moisture from exhaled gas by the patient, and the use of TI of the branches of the breathing circuit may increase the humidity and temperature values of the inhaled gas.

**3-OBJECTIVES**

The objectives of this study are to evaluate the temperature and humidity of the inhaled gases from a low-flow breathing system of the Dräger Fabius GS Premium® anesthesia workstation and to compare the effects of adding TI or HME to the breathing circuit on the temperature and humidity of the inhaled gases from this anesthesia workstation.

**4-PATIENTS AND METHODS**

This study will be performed at Sao Paulo State University Hospital (UNESP, Botucatu, Brazil) and after approval by the Institutional Review Board (Human Research Ethics Committee of the Botucatu Medical School-UNESP), written informed consent will be obtained from all of the patients included in the study. We will evaluate 44 adult (18 to 64 years old) afebrile (T < 37°C) women with a body mass index from 20 to 30 kg.m-² with ASA physical status I or II and scheduled for elective open abdominal gynecologic surgery (hysterectomy or oophorosalpingectomy) with at least 2 hours of anesthesia duration. Patients with signs and symptoms of pulmonary or cardiac disease or a body mass index > 30 kg.m-² will be excluded from the study.

**4.1 Study design**

The patients will be randomly allocated by sequentially numbered sealed envelope assignment into four groups (11 women per group), according to the use of a low-flow breathing circuit with TI or an HME, as follows: control group, without TI or HME; TI group, with TI and without HME; HME group, without TI and with HME; and TIHME group, with TI and HME. An anesthesiologist who will be not involved in the perioperative management of the patients will print 44 group identification tags (11 for each group) and will place these tags into 44 opaque envelopes (one identification tag per envelope). The same anesthesiologist then will seal, mix and sequentially number the envelopes in ascending order. Just before each anesthesia induction, one envelope will be opened following the sequential order to identify the study group.

**4.2 Anesthesia protocol**

A Dräger Fabius GS Premium anesthesia workstation will be used in all cases. Before each anesthetic procedure, the tubes of the anesthesia breathing system will be replaced by clean and dry silicone corrugated tubes of the same length (1.5 m; Dräger Medical, Lübeck, Germany). The CO2 canister (1.5 L) of the anesthesia machine will be filled with fresh soda lime (Drägersorb 800 Plus, Dräger, Lübeck, Germany) before each case. The tubing system, including the CO2 absorber, has an internal volume of 4.5 L. In the TI and TIHME groups, the branches of the breathing circuit will be covered by three layers of aluminum sheets. In the HME and TIHME groups, a hygroscopic HME (Venticaire model 038-41-355; Flexicare Medical Limited, Mountain Ash, UK) will be placed between the Y-piece of the breathing circuit and the tracheal tube.

Upon arrival to the OR, and after 8 hours of fasting, the patients will receive standard clinical monitoring with an electrocardiogram (DII and V5 leads), peripheral oxygen saturation (SpO2), noninvasive arterial blood pressure measurements, a neuromuscular blockade monitor (TOF-watch SX, GPV Elbau Electronics A/S, Aars, Denmark) and a cerebral state index (CSI®) (Danmeter, Biometer International, Odense, Denmark).

An intravenous (IV) line will be inserted with a 20 or 18-G catheter and the patients will receive 3 mg midazolam via IV. Fluid deficits will be replaced with lactated Ringer’s solution at 10 mL.kg-1.h-1. In all of the patients, the fluids will be maintained at the OR temperature. All of the patients will receive active skin-surface warming with a specific blanket on the lower limbs using a warming device (Bair Hugger®, model 750, Arizant Healthcare, Minneapolis, MN) set to delivery forced-air at 43°C following anesthesia induction and lasting until the end of the surgery.

Total intravenous anesthesia will be induced with a target controlled infusion (TCI) of remifentanil (50 µg.mL-1), using a computer-controlled infusion pump (Alaris, Cardinal Health, Rolle, Switzerland) programmed with the Minto adult pharmacokinetic model for remifentanil21.Two minutes later, a TCI of 1% propofol will be administered using a computer-controlled infusion pump (Diprifusor, Fresenius Vial, Brezens, France) programmed with the Marsh adult pharmacokinetic model for propofol22. The initial target remifentanil plasma concentration will be set at 6.0 ng.mL-1, and the propofol plasma concentration will be set at 4.0 µg.mL-1. An IV bolus of cisatracurium besylate (0.15 mg.kg-1) will be given to facilitate orotracheal intubation. The target propofol and remifentanil concentrations will be maintained between 3.0-5.0 µg.mL-1 and 4.0-8.0 ng.mL-1, respectively, to maintain a systemic arterial blood pressure and cardiac rate within ± 20% of baseline and CSI values between 40 and 50. Additional cisatracurium doses (0.05 mg.kg-1) will be provide, when necessary.

After tracheal intubation, a FGF of 2.0 L.min-1 (1.0 L.min-1 of O2 in 1.0 L.min-1 of air) will be supply to the circle breathing during the first 5 minutes and then adjusted to 1.0 L.min-1 (0.5 L.min-1 of O2 in 0.5 L.min-1 of air). The lungs will be mechanically ventilated using the volume-controlled mode of the Fabius anesthesia workstation with a tidal volume of 8 mL.kg-1. The respiratory rate will be adjusted to maintain an end-tidal carbon dioxide pressure (PetCO2) of approximately 35 mm Hg. The inspiratory and expiratory oxygen concentrations, PetCO2 and ventilation variables will be monitored with the Fabius built-in monitor.

**4.3 Measurement of temperature and humidity of the gases**

The primary outcomes temperature and humidity of the gases will be intermittently measured using a rapidly responding electronic digital thermo-hygrometer (Vaisala Humicap® Hand-Held Humidity and Temperature Meter HM 70, Helsinki, Finland) that will be connected by a T-piece between the Y-piece of the breathing circuit and the tracheal tube in the control and TI groups, and between the HME and the tracheal tube in the HME and TIHME groups, and it will be connected to the inspiratory limb outlet close to the anesthesia workstation in all of the groups. The thermo-hygrometer operates on a capacitive principle and has a reported accuracy of ± 2.0% for RH and ± 0.2°C for temperature. The temperature and humidity of the gases are altered with the respiratory cycle phases and are lower in the inspiratory phase. We will record the minimal temperature and RH values averaged over 4 respiratory cycles after 10, 30, 60, 90, and 120 minutes of connection between the patient and the respiratory circuit after tracheal intubation. The AH values will be calculated using the thermo-hygrometer software with the formula AH = (3.939 + 0.5019T + 0.00004615T2 + 0.0004188T3) × RH/100, in which AH is the absolute humidity (mg H2O.L-1), T is the temperature (°C), and RH is the relative humidity (%).

The secondary outcome intraoperative distal esophageal (core) temperature will be measured after tracheal intubation using a thermocouple sensor (Mon-a-therm 90,044®, Mallinckrodt Medical, Veracruz, Mexico). The thermocouple sensors for the esophagus and OR temperatures will be attached to a 2-channel electronic thermometer (4070, Mallinckrodt Medical, St. Louis, MO).

Postoperative analgesia will comprise 0.1 mg.kg-1 morphine, 100 mg tramadol and 100 mg cetoprofen IV, which will be provided 15 minutes before the end of the surgery. The residual neuromuscular blockade will be reversed with 30 µg.kg-1 of neostigmine and 10 µg.kg-1 of atropine IV, if necessary. Tracheal extubation will be performed after full reversal of the neuromuscular blockade. All of the patients will be transferred to the Postanesthesia Care Unit.

**4.4 Statistical analysis**

The sample size of the groups was calculated based on data found in the literature regarding the humidification of gases during anesthesia7,17 and assuming an AH minimum detectable difference of 5.0 mg H2O.L-1 among the groups, with an expected standard deviation (SD) of residuals of ± 3.0 mg H2O.L-1 as significant. For 80% power and considering the risk of a type I error as α of 0.05 or less and of committing type II error as β of 0.20 or less, 9 patients in each group would be required. Since missing data of patients can occur during the study, 11 patients in each group will be enrolled.

The normal distribution of the data will be confirmed using Lilliefors tests. The anthropometric variables will be compared among groups by analysis of variance (ANOVA). The AH, RH, and temperature values will be compared among the groups at different time points by repeated measured ANOVA (Profile Analysis). In this analysis, the following hypotheses will be tested: there was no interaction between groups and time points, and there was no difference between mean groups over time. This analysis will be followed by Tukey’s test for pairwise comparisons. Pearson’s coefficient will be used for the correlation analysis between the OR and inhaled gas temperatures in all of the groups.

The statistical analyses will be performed using the Statistical Package for the Social Sciences (Windows Software, version 17.1; SPSS Inc., Chicago, IL). For all analyses, *P* < 0.05 will be considered statistically significant.

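### The planned repeated-measures ANOVA uses only patients with all five readings, yet the protocol expects missing data and its 2-hour criterion does not secure the 120-minute reading

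*Protocol*

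**What the plan says.** Protocol section 4.4 plans for a difference in absolute humidity (AH) of 5.0 mg H2O/L with a residual SD of 3.0, 80% power and α of 0.05. It concludes that "9 patients in each group would be required". It then adds two per group: "Since missing data of patients can occur during the study, 11 patients in each group will be enrolled". No rate of missing data is given, and no rule for a patient who has some readings but not all.

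The same section fixes the method for AH, relative humidity (RH) and temperature: groups are compared "at different time points by repeated measured ANOVA (Profile Analysis"), with tests of the group-by-time interaction and of group means over time, followed by Tukey's test.

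Section 4.3 makes gas temperature and humidity the primary outcomes and times the readings "after 10, 30, 60, 90, and 120 minutes of connection between the patient and the respiratory circuit", after intubation. Section 4 admits women scheduled for surgery "with at least 2 hours of anesthesia duration". Section 4.2 places remifentanil, propofol two minutes later and cisatracurium before intubation.

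**The concern.** Classical profile analysis treats each patient's five readings as one vector, and the usual repeated-measures procedure drops a patient whose vector has a gap. The chosen method therefore discards valid primary-outcome readings in the very situation the protocol expects.

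The design also makes one gap more likely than the others. The duration criterion and the measurement schedule run on different clocks. Counted from induction, anesthesia starts before connection to the circuit, so a patient can meet the 2-hour criterion exactly and still have less than 120 minutes of connection. The criterion also concerns scheduled cases, while actual duration is unknown when the envelope is opened just before induction (section 4.1). Nothing says what happens if a case ends before the last reading.

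At stake is precision in a trial of 11 per group and, if enough cases are incomplete, the planned power.

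**Working it through.** **Inputs.** From section 4.4: difference 5.0, SD 3.0, α 0.05, power 80%, 9 needed and 11 enrolled per group. From section 4.1: four groups. From section 4.3: five readings. The missing-data rates and between-time correlations below are assumptions, because the protocol gives neither.

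**1. The plan's own figure.** The protocol does not name its formula. A one-way ANOVA F test with four groups, two means 5.0 apart and the other two midway, has noncentrality λ = n × 5² / (2 × 3²) with 3 and 4n − 4 degrees of freedom. At n = 9, λ = 12.5 and power is 0.806. At n = 8, power is 0.745. So 9 per group reproduces.

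**2. What the allowance covers.** 11 − 9 = 2 incomplete patients per group, or 2/11 = 18.2%. Power by complete patients per group:

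| Complete per group | 11 | 10 | 9 | 8 | 7 |
|---|---|---|---|---|---|
| Power | 0.893 | 0.855 | 0.806 | 0.745 | 0.670 |

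**3. Complete-case losses if only the 120-minute reading is missing (assumed rates).** Expected complete patients per group are 11 × (1 − rate). The last column is the binomial probability that a group of 11 keeps at least 9, raised to the fourth power.

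| Patients lacking the 120-min reading | Expected complete per group | Power at that n | Chance all four groups keep ≥ 9 |
|---|---|---|---|
| 5% | 10.5 | 0.87 | 0.94 |
| 10% | 9.9 | 0.85 | 0.69 |
| 20% | 8.8 | 0.80 | 0.15 |
| 30% | 7.7 | 0.72 | 0.01 |

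**4. Precision given up when two of 11 per group lack only the 120-minute reading.**

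- At 10 to 90 minutes all 11 patients were measured but only 9 are used. The variance of a group mean is inflated by 11/9 = 1.22. A mixed model on all available readings avoids this.
- At 120 minutes the earlier readings carry partial information. Under compound symmetry with correlation ρ, the share of the last reading's variance explained by the other four is R² = 4ρ² / (1 + 3ρ). The large-sample variance ratio, mixed model to complete cases, is (1 − R²) + R² × 9/11.

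| ρ (assumed) | R² | Variance ratio at 120 min |
|---|---|---|
| 0.5 | 0.40 | 0.93 |
| 0.7 | 0.63 | 0.89 |
| 0.85 | 0.81 | 0.85 |

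The gain at 120 minutes is thus 7% to 15% in variance, or about 4% to 8% in standard error.

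**The case against.** The strongest reply is that the protocol has already paid for this. Losing two of 11 leaves exactly the 9 it requires, with power 0.806; the 22% is measured against 11 complete patients, a number the calculation never relied on. That stands. A reader might infer that the trial is underpowered, but the documents do not support it: planned power falls short only beyond two incomplete patients in a group, and no loss rate is given.

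Deletion of incomplete patients is also not written anywhere. It is the default behaviour of the method, and a rule for partial data could sit in an analysis plan that is not shown. That limits the point without removing it, because the protocol itself fixes the method that creates the problem.

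The sentence on missing data may mean loss of whole patients. For someone with no readings, extra enrolment is the right answer and a mixed model recovers nothing. The point applies to partial loss only.

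The clock mismatch affects only cases at or a little above 2 hours. The protocol defines neither the start nor the end of anesthesia and does not give the interval from induction to connection, so the number affected is unknown.

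Finally, a reader might infer bias, since the analysed set would be selected on length of surgery, known only after randomisation. Nothing in the protocol links duration to group or to inspired humidity at a fixed minute. If the loss is unrelated to both, complete-case means are unbiased and the cost is efficiency alone.

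**Conclusion.** The point holds as an avoidable inefficiency built into the stated method, not as an error in the sample size or a demonstrated bias. With two incomplete patients per group, valid readings are discarded and the variance of group means at 10 to 90 minutes is 22% higher than it need be, with a smaller loss at 120 minutes (7% to 15%, under assumed correlations of 0.5 to 0.85 and compound symmetry). Planned power is kept in that case. Beyond two per group it is not: 0.745 with 8 complete patients and 0.670 with 7.

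This rests on three things: the standard complete-case form of the ANOVA, partial rather than whole-patient loss, and a duration criterion counted from induction. The change is worth making because it is cheap, tests the same hypotheses and gives essentially the same answer if the data turn out complete.

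**What to change.** In section 4.4, replace the profile-analysis ANOVA for AH, RH and temperature with a linear mixed model:

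- REML estimation, with fixed effects for group, time and group × time.
- One prespecified covariance structure, for example unstructured. AR(1) in its usual form does not suit these times, because the first interval is 20 minutes and the others 30.
- Kenward-Roger or Satterthwaite degrees of freedom, one of them named in advance. An unstructured matrix for five times has 5 × 6 / 2 = 15 parameters, estimated from 44 patients, so a small-sample method is needed.
- All randomised patients with at least one reading, and Tukey-adjusted pairwise contrasts.

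Also reconcile the duration criterion in section 4 with the measurement clock in section 4.3, so that scheduled duration is counted as time connected to the circuit. This reduces missed 120-minute readings but cannot guarantee them, since actual duration may differ from the schedule; the model handles what remains.

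Cost: slightly more analysis work (SPSS, the named package, has a mixed-model procedure), reliance on a missing-at-random assumption that should be stated, and possibly a few short cases not enrolled. The figures of 9 and 11 per group need not change.

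### The group comparison in section 4.4 omits operating room temperature, which the protocol calls a direct influence on the outcome and has to measure, so precision is lost and chance imbalance stays uncorrected

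*Protocol*

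**What the plan says.** The Introduction states: "The operating room (OR) temperature directly influences the heat and moisture of the inhaled gases at different anesthesia workstations". It attributes this to the poor thermal insulation of the silicone tubing. The Study Hypothesis repeats the idea for this workstation, describing the minimum humidity level of the inspired gas as something "which can be directly influenced by the OR temperature".

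Section 4.3 provides for the measurement: "The thermocouple sensors for the esophagus and OR temperatures will be attached to a 2-channel electronic thermometer". It gives no reading times for OR temperature; the 10 to 120 minute schedule is written for the gas readings.

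Section 4.1 allocates 44 women to four groups of 11 by sealed envelope and describes no stratification. Nothing in the protocol says that OR temperature is held fixed.

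Section 4.4 compares AH, RH and gas temperature among groups by repeated-measures ANOVA (profile analysis), followed by Tukey's test. The two null hypotheses are that "there was no interaction between groups and time points, and there was no difference between mean groups over time". No covariate is named. OR temperature appears in the analysis once, in a Pearson correlation with inhaled gas temperature in all groups.

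**The concern.** The protocol identifies a cause of variation in its primary outcomes, has to measure it in every group for the correlation, and then leaves it out of the comparison that answers the study question. The separate correlation does not fill the gap. It neither adjusts the group differences nor reduces the error term, and it covers gas temperature but not AH or RH.

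Two things are at stake. Variation in the outcome that comes from room temperature stays in the error term, so the intervals for the effects of thermal insulation (TI) and the heat and moisture exchanger (HME) are wider than they need be. And with 11 patients per group, mean OR temperature will differ between groups by chance in any one realisation of the trial, with nothing in the model to correct for it.

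OR temperature is read during the case, after allocation. Wrapping the circuit or adding an HME should not plausibly change the temperature of the room, so it remains acceptable as a covariate.

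**Working it through.** **Inputs from section 4.4.** The target difference: "assuming an AH minimum detectable difference of 5.0 mg H2O.L-1 among the groups". The SD: "with an expected standard deviation (SD) of residuals of ± 3.0 mg H2O.L-1 as significant". Power and alpha: "For 80% power and considering the risk of a type I error as α of 0.05 or less". There are four groups, with 9 per group required and 11 enrolled.

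**Assumed input.** r is the correlation between OR temperature and the outcome within groups. The documents give none, so 0, 0.3, 0.5 and 0.7 are shown. The calculations treat AH as one value per patient.

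**1. Reproducing the plan's figure.** One-way ANOVA with four groups, two means 5.0 apart and the other two midway, has noncentrality λ = n × 5.0² / (2 × 3.0²).
- n = 8: λ = 200/18 = 11.1, power 0.745.
- n = 9: λ = 225/18 = 12.5, power 0.806. This reproduces the protocol's 9 per group.
- n = 11: λ = 275/18 = 15.3, power 0.893.

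**2. Chance imbalance.** The difference between two group means of OR temperature has SD = √(2/11) = 0.43 of the between-case SD. The average gap between the highest and lowest of the four group means is 0.62 SD (simulation). A one-SD pairwise imbalance shifts the AH difference by r × 3.0 × 0.426, which is 0.38, 0.64 or 0.90 mg/L at r = 0.3, 0.5 or 0.7. The average highest-to-lowest gap shifts it by r × 3.0 × 0.62, which is about 0.6, 0.9 or 1.3 mg/L. The target difference is 5.0 mg/L. The full unadjusted standard error of a pairwise difference is 3.0 × √(2/11) = 1.28 mg/L, which already contains this component.

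**3. Effect of adjustment.** Residual SD becomes 3.0 × √(1 − r²), with one error degree of freedom fewer. Pairwise power is for the 5.0 mg/L contrast with Tukey's critical value (20,000 simulated trials per row).

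| Model | Variance removed | Residual SD | F-test power, n = 9 | F-test power, n = 11 | Detectable difference, n = 11, 80% power (mg/L) | Tukey pairwise power, n = 11 |
|---|---|---|---|---|---|---|
| Unadjusted | – | 3.00 | 0.806 | 0.893 | 4.4 | about 0.885 |
| Adjusted, r = 0.3 | 9% | 2.86 | 0.844 | 0.920 | 4.2 | 0.909 |
| Adjusted, r = 0.5 | 25% | 2.60 | 0.911 | 0.963 | 3.9 | 0.956 |
| Adjusted, r = 0.7 | 49% | 2.14 | 0.983 | 0.996 | 3.2 | 0.995 |

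**4. Cost if the covariate is useless.** At r = 0, Tukey pairwise power goes from 0.886 to 0.874 at n = 11 and from 0.787 to 0.770 at n = 9, a loss of 1 to 2 points.

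**5. Does imbalance weigh most on the TI comparison?** Take an OR temperature slope of 1 in the control group and b in the TI group. The imbalance SD is √((1 + b²)/11): 0.43 at b = 1, 0.34 at b = 0.5 and 0.30 at b = 0. If insulation works as intended, the TI versus control contrast is less exposed than one between two uninsulated groups with equal slopes.

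**The case against.** Nothing in section 4.4 is invalid. Allocation is randomised, so the unadjusted comparison is unbiased on average and its P values already allow for chance imbalance. The sample size also meets its own 80% target without a covariate. This stands, and it limits the point to efficiency. A reader might infer that the TI and HME effects will be biased or the tests wrong; the documents do not support that.

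The gain is also undocumented. A reader might conclude that adjustment is worth 15 to 22 patients per group, since 11/(1 − r²) is 14.7 at r = 0.5 and 21.6 at r = 0.7. At r = 0.3 the same formula gives only 12.1. The Introduction's statement concerns other workstations, and the protocol says that this one warms the gas twice and has not been investigated. A strong correlation cannot be assumed.

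It is tempting to say that the TI comparison suffers most, because insulation acts on heat loss to the room. The fifth step of the working shows that this mechanism points the other way.

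Unequal slopes are the best technical objection. TI may flatten the OR temperature slope, and in the HME groups the gas is measured on the patient side of the device. A single common slope could then be wrong. This calls for an interaction check; it does not justify omitting the covariate.

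Finally, covariates are often left to a statistical analysis plan, which is not at hand. But section 4.4 states the model and its hypotheses and defers nothing. If such a plan adds the covariate, the point is met.

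**Conclusion.** The point holds as a matter of precision. The protocol fixes a group comparison without a covariate that it describes as a direct influence and must measure in all groups. The size depends on an unknown correlation: the gain is slight at 0.3 (F-test power 0.893 to 0.920 at 11 per group) and clear at 0.5 or more (0.963 and above). The loss if the covariate proves useless is 1 to 2 points of pairwise power. The change is worth making, but the trial does not fail without it.

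Two assumptions matter. The first is that OR temperature is available for every patient. This is inferred from the sensor in section 4.3 and the correlation in section 4.4, and no reading schedule is given. The second is that the 3.0 mg/L residual SD includes variation due to OR temperature. If it already excludes it, the unadjusted SD would be 3.0/√(1 − r²), that is 3.1, 3.5 or 4.2 mg/L at r = 0.3, 0.5 or 0.7, and the unadjusted power above would be overstated.

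**What to change.** In section 4.4, before any outcome data are seen:
- Add the per-case mean OR temperature, centred at its overall mean, as a covariate in the repeated-measures model for AH, RH and gas temperature. The per-case mean avoids a time-varying covariate, which the named profile analysis does not provide for.
- Report adjusted group differences, with Tukey's comparisons made on the adjusted means, and give the unadjusted differences as sensitivity.
- Prespecify a check of the group by OR temperature interaction, because TI and HME may change the slope. If group slopes are fitted, report the differences at the overall mean OR temperature and say so, since they then depend on the value chosen.

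In section 4.3, state when OR temperature is read in each case.

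The cost is one degree of freedom for a common slope, or four in place of one if each group has its own. No measurement is needed beyond those the planned correlation already requires. Fixing the choice in advance also prevents deciding on adjustment after seeing the results.
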